### Interventions

The participants will receive a total of 24 treatments in 12 weeks. The interventionists, who hold a PhD, must have at least 10 years of experience with Tuina treatment and be skillful in healthcare education for the participants. They are also required to have passed a clinical test to ensure consistency of the trial. The clinical test primarily includes the time of Tuina, the positioning of the treatment site, and the application of specific Tuina manipulation types. The standard operating procedures primarily include Tuina’s time, treatment site, and manipulation category, as well as the time and content of health education. In the process of Tuina or Education intervention, the two groups will not allow any concomitant medications or other interventions. However, concomitant medications or other interventions can be used during subsequent follow-up, and the treatment will be recorded in detail.

### Tuina group

The selected acupoints for the Tuina treatment include EX-LE02 (heding), EX-LE04 (neixiyan), EX-LE05 (xiyan), GB34 (yanglingquan), SP10 (xuehai), ST34 (liangqiu), ST32 (futu), BL40 (weizhong), BL57 (chengshan), GB31 (fengshi), and Ashi acupoints around the knee joint. An ashi point is a temporary acupoint where sensation of acid, distension, and pain exist, which can appear anywhere in knee joints [61].

Referring to previous studies [44, 62–64], the Tuina procedures are as follows. First, the patients will be in a supine position. The doctor stands on the side of the patient. The Pressing and Kneading Manipulation of Tuina is applied to the anterior acupoints around the affected knee joint for 10 to 15 min by using the thumb to achieve Deqi sensation, which is commonly regarded as an indicator of manipulation efficacy [65, 66]. Second, the patients will be in a prone position. Then, the physician will perform the same manipulation on the patient’s posterior acupoints around the affected knee joint for 10 to 15 min. The purpose is to relax sinews and activate collaterals according to the theory of TCM. Every patient will receive 30 min of manipulation per treatment with two treatments per week for 12 weeks.

### Education group

The Osteoarthritis Research Society International (OARSI) and the European Society for Clinical and Economic Aspects of Osteoporosis, Osteoarthritis and Musculoskeletal Diseases (ESCEO) updated the guidelines on KOA in 2019 [67]. In the guidelines, both organisations recognised the efficacy of health education in the treatment of KOA. Therefore, in this experiment, we will use health education to implement interventions in a group of subjects.

The education intervention will be given to the participants with two sessions per week. The first health education session is a group meeting using a PowerPoint presentation, which will last 30 min. An educational booklet and a video will be provided to the patients to accomplish the home-based online e-learning module. The later sessions will be conducted as one-to-one communication focused on personal needs to guide patients to implement the key education in their lives. The programme includes two broad components: (1) introduce key concepts of pain biology, and (2) present specification of recovery.

Each patient will be given an introduction about the underlying mechanisms, predisposing factors, and prognosis of KOA. Pain will be explained as the conscious part of the response, which can be influenced by many factors as a protective output [68]. Interventionists will formulate a specification of daily routines for patients, for example, keeping the knees warm, keeping a healthy diet and preventing obesity [69], maintaining beneficial posture and abandoning bad habitual posture [70], and avoiding too much work.

### Concomitant medications and other interventions

Patients with KOA will be instructed not to take any caffeine (e.g., tea and coffee), as well as other medications, weight-loss techniques, or physical activity to avoid confounding interference for the analgaesic effect of the intervention in the two groups. In cases of severe knee pain, ibuprofen (300 mg per capsule with sustained release) will be allowed as rescue medication and should be recorded on a knee-pain diary. After the end of the study, patients will be taught weight-loss techniques and physical activity. Patients are also asked to record the name, dose, date, frequency, and exact time of the medications used, as well as to report to the researcher if they take any medications during the study. Patient adherence will be maintained and monitored by good communication between the therapist and patient and by constant reminders.

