### Suspension criteria

Are unsuitable to continue to participate in the study owing to adverse events or serious adverse events during the trialAre unsuitable to continue to participate in the study because of serious deterioration of disease or some complications and special physiological changesUses concomitant medication during the 12-week treatment period is a suspension criteria. Non-compliance to concomitant interventions will be monitored by daily dairies and WeChat queries.

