#### Primary outcome measurement

The primary outcome measurement is VAS [74]. VAS is used to assess the current degree of pain. VAS is a 10-point scale selected to quantitatively measure the level of KOA pain during the study, for which 0 means no pain and 10 means unbearable pain. The VAS mean scores will be assessed by repeated longitudinal analysis. The single timepoint of the primary interest for the comparison is week 12.

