### Statistical analyses

Clinical data will be analysed through the intention-to-treat assumption. For all outcomes, we use longitudinal models where participant outcomes and treatments are collected at a multiple follow-up times. Moreover, participants who meet the suspension criteria will be removed from the trial, and the modified intention-to-treat analysis will be adopted. For the missing data, several sensitivity analyses will be conducted to evaluate their effects on the results of the experiment. All analyses were performed with SPSS 21.0 statistical software (IBM, Armonk, NY, USA) by statisticians who are blinded to the group allocation.

The baseline characteristics will be expressed with descriptive statistics for the two groups, which are reported as the mean ± standard deviation. A Kolmogorov–Smirnov test with Lilliefors correction will be used to analyse all quantitative variables to determine whether they follow a normal distribution. Parametric statistics (Tukey test) or nonparametric statistics (Wilcoxon rank-sum test) will be used for the within- and between-group analyses in accordance with the results of the homogeneity and normality analyses. When the initial homogeneity and normality of data distribution are found, repeated-measure ANOVA will be implemented, or the Friedman test and Kruskal–Wallis test will be used when initial homogeneity but non-normality of data distribution is found, or only linear mixed model will be adjusted for age and gender if the initial homogeneity is not found. Adverse events in each group will be documented as percentage for safety assessments by using the chi-square test or Fisher’s exact test. Statistical significance is defined as *P* < 0.05, and the 95% confidence interval will be reported.

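### Rescue ibuprofen is permitted for severe knee pain, yet taking it during the 12 weeks of treatment meets the rule for removal from the trial, so who contributes a week-12 VAS depends on pain

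*Protocol article*

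**What the plan says.** Four sections of the Protocol article bear on a participant who takes a painkiller during treatment.

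- **Concomitant medications and other interventions:** "In cases of severe knee pain, ibuprofen (300 mg per capsule with sustained release) will be allowed as rescue medication". Its use is to be entered in a knee-pain diary. No period is named.
- **Interventions:** "In the process of Tuina or Education intervention, the two groups will not allow any concomitant medications or other interventions". The same section then relaxes the rule for later: "concomitant medications or other interventions can be used during subsequent follow-up".
- **Suspension criteria:** use of concomitant medication in the 12-week treatment period is itself a suspension criterion. The next sentence adds: "Non-compliance to concomitant interventions will be monitored by daily dairies and WeChat queries". Ibuprofen is neither named nor exempted.
- **Statistical analyses:** the section opens with "Clinical data will be analysed through the intention-to-treat assumption" and then says that "participants who meet the suspension criteria will be removed from the trial, and the modified intention-to-treat analysis will be adopted". The modified set is not defined further.

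The primary outcome is VAS for current pain. Under Primary outcome measurement: "The single timepoint of the primary interest for the comparison is week 12". That is the end of the period in which the medication ban applies.

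**The concern.** The protocol gives two answers to a question that staff must settle while treatment is running: does a participant who takes rescue ibuprofen stay in? One section permits the drug. Three others, taken together, remove whoever uses it.

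The trigger makes this more than a wording problem. Rescue is allowed only for severe knee pain, and the primary outcome is pain. A rule that removes rescue users therefore tends to remove participants who are doing badly, so those who remain are no longer the randomised groups. Rescue use could well differ between arms: the sample size section expects a VAS improvement of 3 with Tuina and 0.7 with education, and neither participants nor therapists are blinded. Removals mainly from the Education group would make that group look better and shrink the apparent benefit of Tuina. Removals mainly from the Tuina group would inflate it. The problem is selection bias, not loss of power.

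**Working it through.** **Step 1. Do the rules conflict?**

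| Question | Concomitant medications | Interventions | Suspension criteria | Statistical analyses |
|---|---|---|---|---|
| Is ibuprofen for severe pain allowed in weeks 0 to 12? | Yes, with diary entry | No medication allowed | Use is a suspension criterion | – |
| Does the user stay in the trial and the analysis? | Not stated | Not stated | Suspended | Removed; modified intention-to-treat |

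Two readings might reconcile them.

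- *Rescue applies only in follow-up.* The Interventions section already permits any concomitant medication in follow-up, so a rescue permission would hardly be needed there. The permission also comes directly after a ban whose stated purpose is to avoid confounding the analgesic effect of the intervention, which concerns the treatment period.
- *Rescue ibuprofen is not a concomitant medication.* It is listed under that heading, and neither of the other two sections exempts it.

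**Step 2. How far could removal move the primary contrast?**

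The plan gives no figure for this, so there is none to reproduce. Inputs from the Sample size section: SD 2.1; planned difference 3 − 0.7 = 2.3; 30 per arm. Assumption: VAS change is normal within each arm.

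If the k least-improved of n = 30 are removed from one arm, its mean change rises by

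shift = SD × (sum of the k largest expected standard normal order statistics) / (n − k).

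For n = 30 the three largest expected order statistics are 2.043, 1.616 and 1.365.

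- k = 1: 2.1 × 2.043 / 29 = 0.148, and 0.148 / 2.3 = 6%.
- k = 3: 2.1 × (2.043 + 1.616 + 1.365) / 27 = 2.1 × 5.023 / 27 (sum of the unrounded values) = 0.391, and 0.391 / 2.3 = 17%.

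A simulation of 400,000 draws gave 0.147 and 0.389. The large-sample form SD × φ(z)/(1 − p), with z the normal quantile at p, gives 2.1 × 0.0742 / 0.9667 = 0.161 for p = 1/30 and 2.1 × 0.1755 / 0.9 = 0.409 for p = 3/30.

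These are upper bounds, because rescue users need not be exactly the least-improved. If rescue use follows a pain-status score that correlates 0.5 with VAS change (assumption), the shifts halve:

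- k = 1: 0.148 × 0.5 = 0.074 (3%).
- k = 3: 0.391 × 0.5 = 0.195 (8%).

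**Step 3. What if both arms face the same removal threshold?**

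Take change as Normal(3, 2.1) for Tuina and Normal(0.7, 2.1) for Education. Remove anyone whose pain-status score, on the same scale, falls below a common cut-off c. In each arm the kept mean rises by ρ × 2.1 × φ(a)/(1 − Φ(a)), with a = (c − mean)/2.1 and ρ the correlation between that score and VAS change.

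| Cut-off c | Removed, Tuina vs Education | Expected difference, ρ = 1.0 | Expected difference, ρ = 0.5 |
|---|---|---|---|
| −2 | 1% vs 10% | 1.94 | 2.12 |
| −1 | 3% vs 21% | 1.68 | 1.99 |
| 0 | 8% vs 37% | 1.37 | 1.84 |

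If the planned effect is real, a common threshold removes more of the Education group, and the planned 2.3 shrinks. The cut-offs are illustrative.

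**The case against.** The best opposing case has five parts.

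1. *A specific permission may override a general ban.* The sentence after the suspension criterion speaks of non-compliance, and rescue taken as allowed is arguably not that. This is a possible intention, but the protocol does not state it, and two members of staff could apply the rule differently. It argues for writing the exemption down.

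2. *The modified set is undefined.* A longitudinal model might keep a removed participant's baseline and week-6 scores, and sensitivity analyses for missing data are planned. This is correct as far as it goes. But someone removed before week 12 supplies no week-12 VAS, and an analysis plan cannot recover a value that was never collected. Sensitivity analyses do not change the primary population either.

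3. *The effect is probably small.* The standard error of the difference at 30 per arm is 2.1 × √(2/30) = 0.54, so every one-arm shift in Step 2 is below one standard error. The eligibility criteria take Kellgren–Lawrence I–II knees and exclude recent analgesic use, so rescue may be rare. The more plausible direction, more removals from Education, works against Tuina. This stands as a limit on size. A small systematic error is still an error, and the direction cannot be assured in advance.

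4. *Keeping rescue users has a price.* Ibuprofen may lower their week-12 VAS, and the protocol restricts analgesics partly because of brain imaging. This is a fair trade-off. It is minor next to removing people because of their pain, and retention follows the intention-to-treat principle that the protocol itself states.

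5. *The change is not quite free.* Retained participants must be assessed when they would otherwise have left, and the trial is recruiting. This stands and is reflected in the cost.

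**Conclusion.** The concern holds. Taken as written, the rules make a participant removable for using a drug that the protocol permits for severe pain, and this happens before the primary pain assessment. Exclusion from the week-12 comparison can therefore depend on the outcome.

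The size cannot be known from the document, because it gives no rescue rate. The one-arm shift for 1 to 3 removals out of 30 is about 0.07 to 0.39 VAS points, or 3% to 17% of the planned difference. This range rests on normal change scores with SD 2.1, removals from one arm only, and a correlation between rescue use and VAS change of 0.5 to 1. Similar removals in both arms would largely cancel, while heavier and unequal removal would do more. The conflict in the text is certain; the bias is conditional on rescue being used and the removal rule being applied. This should be fixed. Other grounds for suspension are outside this point.

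**What to change.** State one rule and carry it through:

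- **Suspension criteria and Interventions:** exempt recorded rescue ibuprofen, taken as the concomitant-medication section allows, from the ban and from the suspension criterion.
- **Statistical analyses:** add a sentence that rescue use neither ends outcome collection nor removes a participant from the primary intention-to-treat analysis of week-12 VAS.
- **Reporting:** give rescue use by arm, from the diary already planned.

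The cost is an exemption in two sections and one added sentence. No new instrument or visit is needed, because the week-12 assessment and the diary are already scheduled, but rescued participants must be kept in and assessed at those visits. Under Quality control, the steering and ethics committees must be informed of the change. As the trial is recruiting, the change should come soon: week-12 scores of anyone already removed for rescue use may not be recoverable.

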### Safety evaluation

The participants’ conditions will be carefully monitored by therapists during the process. If adverse events occur, participants with adverse events will stop participating in the trial. Immediate medical care will be provided to any participant experiencing adverse reactions that can lead to hospitalisation, for example fracture or coma. The details will be recorded in the case report forms (CRFs). The ethics committee will conduct an interim analysis and make a decision, which will be determined according to the severity of the adverse events of the participants. For example, conditions that lead to hospitalisation or even life-threatening are severer, whereas conditions such as muscle pain that can heal on their own are milder. Reports will be made to the ethics committee with statements and detailed reasons for trial suspension. The efficacy and safety of the intervention will be evaluated after 6 and 12 weeks of intervention and 48 weeks of subsequent follow-up. Evaluators can also be reformed with the clinical symptoms and AEs whenever the patients meet something important. After an adverse event is determined to be related to the trial plan, the research team will provide treatment costs and corresponding financial compensation for the damage inflicted by the trial plan.

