**Fig. 2 Fig2:**
[figure not shown]
Study schedule for data collection. The informed consent and examination will be conducted after recruitment. Then, matched KOA patients will be randomized into two groups and receive treatment. Both clinical outcomes and MRI scans will be performed at 3 time points. Only clinical data will be collected at 48 weeks of follow-up subsequently. Adverse events will be recorded in the case report form at any time during the study. *VAS* visual analog scale, *SF-MPQ* the Short-Form McGill Pain Questionnaire, *HAMD* Hamilton Depression Scale, *HAMA* Hamilton anxiety scale, *WOMAC* the Western Ontario and McMaster Universities Osteoarthritis Index, *SF-36* the Short Form 36 Health Survey scale

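### The safety section ends trial participation for any adverse event, in conflict with the suspension criteria, and the analysis section then removes suspended participants

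*Protocol article*

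**What the plan says.** Four parts of the protocol article bear on this.

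- **Safety evaluation** gives an unconditional rule: "If adverse events occur, participants with adverse events will stop participating in the trial". It goes on to have the ethics committee "make a decision, which will be determined according to the severity of the adverse events of the participants". It contrasts events that lead to hospitalisation or threaten life with milder ones: "conditions such as muscle pain that can heal on their own are milder".
- **Suspension criteria** give a conditional rule. An adverse event, serious or not, leads to suspension when it makes the participant unsuitable to continue. Deterioration and concomitant medication are separate grounds and are not at issue here.
- **Statistical analyses** opens with "Clinical data will be analysed through the intention-to-treat assumption", but adds that "participants who meet the suspension criteria will be removed from the trial, and the modified intention-to-treat analysis will be adopted".
- **Primary outcome measurement** fixes the key comparison: "The single timepoint of the primary interest for the comparison is week 12". The legend of Fig. 2 says of safety: "Adverse events will be recorded in the case report form at any time during the study".

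Nothing in the article says that a participant stopped for an adverse event stays in scheduled assessment.

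**The concern.** Staff cannot follow both stopping rules. A participant with mild soreness after a session leaves under the safety section, but continues under the suspension criteria unless judged unsuitable.

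The safety rule also ends participation in the trial, not only in the sessions. Read literally, someone stopped before week 12 has no week-12 VAS, no follow-up assessments, and no record of later adverse events. The first event is still recorded and treated.

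The reason for leaving can be caused by the treatment. One arm receives 24 sessions of manual pressing and kneading and the other receives education, so stopping is plausibly more frequent in the Tuina arm. Therapists, who monitor for events, and participants both know the allocation. The Tuina patients left at week 12 would then be those who tolerated it. The removal clause in the analysis section has the same effect on anyone suspended for an adverse event.

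**Working it through.** **1. The texts side by side**

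| Question | Safety evaluation | Suspension criteria |
|---|---|---|
| Trigger | Any adverse event | Adverse event that makes the participant unsuitable to continue |
| Severity or judgement condition | None on the individual | Judgement of unsuitability |
| Mild, self-healing muscle pain | Stops | Continues unless judged unsuitable |

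The severity wording is attached to the ethics committee's decision. The section does not say that a mild event exempts the individual from stopping.

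The removal clause in Statistical analyses refers to the suspension criteria. A participant suspended there for an adverse event is removed. For a participant stopped only under the safety rule, removal from the analysis is not stated, but the week-12 value is missing in any case.

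**2. Power**

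Inputs from Sample size: mean VAS change 3 (Tuina) and 0.7 (Education), SD 2.1, two-sided α = 0.05, power 0.90, 30 randomised per group.

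The planned difference is 3 − 0.7 = 2.3. With these inputs the usual formula gives n = 2(1.960 + 1.282)²(2.1/2.3)² ≈ 17.5, so 18 per group (19 with a t test). The stated 25 is not reproduced. It errs on the safe side, and nothing below depends on it.

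Power of a two-sided t test with difference 2.3 and SD 2.1:

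| Tuina / Education analysed | Power |
|---|---|
| 25 / 25 | 0.967 |
| 20 / 24 | 0.942 |
| 18 / 24 | 0.929 |
| 15 / 24 | 0.900 |

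The 24 is 30 × 0.8, that is, after the planned 20% dropout. Even large extra losses in the Tuina arm leave power at about 0.90.

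**3. Bias over an assumed range**

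The article gives no adverse event rate, so these are assumptions. Let k of 30 Tuina patients be stopped, with mean VAS change m. The other Tuina patients change by 3.0 and Education by 0.7, and only retained patients are compared.

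- Difference among retained patients: 3.0 − 0.7 = 2.3
- Difference among all randomised patients: 2.3 − (k/30)(3.0 − m)
- Overstatement: (k/30)(3.0 − m)

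| m | k = 1 | k = 3 | k = 6 |
|---|---|---|---|
| 3.0 (no worse than the rest) | 0 | 0 | 0 |
| 1.5 | 0.05 | 0.15 | 0.30 |
| 0.7 (same as Education) | 0.08 | 0.23 | 0.46 |

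For example, k = 6 and m = 0.7 gives (6/30) × 2.3 = 0.46, which is 20% of the planned difference. A longitudinal model that uses week-6 data could reduce these figures.

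**The case against.** The strongest reply is that the safety sentence is a loose summary of the suspension criteria. The section grades events by severity, and the grading would do nothing for individuals if every event ended participation. The section dedicated to suspension requires unsuitability. On that reading the any-event rule was never meant, and one sentence needs clarifying. This is possible, but the article does not say it. It also leaves the removal clause in place for everyone suspended for an adverse event, and still no text keeps those people in assessment.

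A second reply is that the removal clause is a separate matter, because it is triggered by the suspension criteria and not by the safety sentence. The trigger is as described. The two still act on the same primary comparison, and correcting the safety sentence alone would not keep suspended patients in the analysis.

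Third, the loss of later safety data is inferred, since the Fig. 2 legend promises recording throughout. That is fair. The loss follows only from reading the end of participation literally, and the texts should be reconciled.

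Fourth, the bias range stops patients in one arm only, whereas the literal rule covers both, and the larger values need many stopped patients with little benefit. This stands as a limit on size. If j Education patients with mean change e were also stopped, the overstatement would become (k/30)(3.0 − m) − (j/30)(0.7 − e), which could be smaller. For scale, the standard error of the difference at 25 per group is 2.1 × √(2/25) = 0.59, above every value in the table.

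Finally, the plan allows for 20% dropout and promises sensitivity analyses for missing data. These can probe the missingness, but they cannot recover a week-12 VAS that was never collected.

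**Conclusion.** The concern holds and should be fixed. The article gives two incompatible rules for stopping after an adverse event. It also declares intention-to-treat and then removes participants suspended for a reason that treatment can cause. The first defect may be a slip of wording; the second remains under either stopping rule.

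The effect on the result cannot be stated, because no event rate is given. Under the assumed one-arm scenarios, the overstatement runs from 0 to 0.46 VAS points against a planned 2.3, and from 0 to 0.23 if no more than 3 of 30 Tuina patients are stopped. The upper values require that stopped patients gain no more than Education patients and that week-6 data are not used. The harm is potential bias and incomplete safety follow-up, not loss of power.

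**What to change.** 1. In Safety evaluation, replace the unconditional sentence with the judgement used in Suspension criteria, applied to sessions only: sessions stop when an adverse event makes the participant unsuitable to continue.
2. State that participants whose sessions stop remain in all scheduled clinical assessments, including week-12 VAS, and in safety follow-up, unless they withdraw consent.
3. In Statistical analyses, state that participants suspended for adverse events stay in the intention-to-treat analysis in their randomised group.

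The cost is a protocol amendment notified to the steering and ethics committees, as Quality control requires, plus a few more attendances at visits already scheduled. No new staff or procedures are needed, and participants are no less protected, because sessions still stop when they should. The trial is described as recruiting, and uncollected assessments cannot be recovered, so the change is worth most if made early.
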